## Abstract

**Background:** The Japan-Multi-domain Intervention Trial for Prevention of Dementia in Older Adults with Diabetes (J-MIND-Diabetes) is an 18-month, multi-centered, open-labeled, randomized controlled trial designed to identify whether multi-domain intervention targeting modifiable risk factors for dementia could prevent the progression of cognitive decline among older adults with type 2 diabetes mellitus (T2DM). This manuscript describes the study protocol for the J-MIND-Diabetes trial.

**Materials and Methods:** Subjects of this trial will comprise a total of 300 T2DM outpatients aged 70–85 years with mild cognitive impairment. Subjects will be centrally randomized into intervention and control groups at a 1:1 allocation ratio using the stratified permuted-block randomization methods. The intervention group will participate in multi-domain intervention programs aimed at: (1) management of metabolic and vascular risk factors; (2) physical exercise and self-monitoring of physical activity; (3) nutritional guidance; and (4) social participation. The control group will receive usual T2DM care and general instructions on dementia prevention. The primary and secondary outcomes will be assessed at baseline, at 6- and 18-month follow-up. The primary outcome is change from baseline at 18 months in a global composite score combining several neuropsychological domains, including global cognitive function, memory, attention, executive function, processing speed and language. Secondary outcomes include: (1) cognitive changes in neuropsychological tests; (2) changes in geriatrics assessments; (3) metabolic control and diabetic complications; (4) changes in blood and urinary markers.

**Discussion:** This trial will be the first trial to demonstrate the effectiveness of multi-domain intervention in preventing cognitive decline in older adults with T2DM at increased risk of dementia in Japan.

**Trial Registration:** UMIN000035911; Registered on the University Hospital Medical Information Network Clinical Trials Registry (UMIN-CTR) 18 February 2019. (https://upload.umin.ac.jp/cgi-open-bin/ctr_e/ctr_view.cgi?recptno=R000040908).

## Introduction

The incidence and prevalence of dementia have been increasing worldwide. The number of people living with dementia is estimated at 46.8 million in 2015, and expected to increase to 131.5 million by 2050 (Prince et al., 2015).

To date, risk factors for dementia that are potentially modifiable throughout lifespan have been reported (Livingston et al., 2020), which include: less education in early life; hearing loss, traumatic brain injury, hypertension, excessive alcohol consumption and obesity in midlife; and smoking, depression, social isolation, physical inactivity, diabetes and air pollution in later life. Among these, ample evidence suggests that type 2 diabetes mellitus (T2DM) is among the important potentially modifiable risk factors. A meta-analysis demonstrated that patients with T2DM are placed at higher risk of incident mild cognitive impairment (MCI), Alzheimer's disease (AD), and vascular dementia (VaD) than those without (Cheng et al., 2012). While multiple underlying mechanisms may account for the significant link between T2DM and dementia, of these, poor glycemic control, hypoglycemia, glycemic variability, and insulin resistance may be of particular interest, in that they may contribute to neurodegenerative pathologies and cerebrovascular disease (Biessels et al., 2006; Strachan et al., 2011). Thus, it remains an urgent priority to formulate successful strategies against cognitive decline and dementia in older adults with T2DM.

Several randomized controlled trials were conducted in this population with a focus on the effects of intensive glycemic control on cognitive function (de Galan et al., 2009; Launer et al., 2011; Koekkoek et al., 2012). However, these studies have failed to provide evidence to support the beneficial effects of intensive glycemic control on cognition, while one study showed the beneficial effect on total brain volume (Launer et al., 2011). Moreover, it is suggested that severe hypoglycemia associated with intensive glycemic control may rather increase the risk of not only cognitive impairment and dementia but cardiovascular events and mortality (Yaffe et al., 2013; Mattishent and Loke, 2016a,b). In light of the available evidence, therefore, the “Glycemic Targets for Elderly Patients with Diabetes” were put forth in 2017 by the Japan Diabetes Society (JDS)/Japan Geriatrics Society (JGS) Joint Committee (Japan Diabetes Society (JDS)/Japan Geriatrics Society (JGS) Joint Committee on Improving Care for Elderly Patients with Diabetes, 2017), which proposed, along with other guidelines/position statements that to achieve appropriate glycemic control and prevent complications of diabetes, care should be exercised to avoid severe hypoglycemia, specifying lower limits for proposed glycemic targets among older adults, particularly those at high risk (i.e., those who have frailty, cognitive impairment, or dementia) (Sinclair et al., 2011, 2018; Dunning et al., 2014; Japan Diabetes Society (JDS)/Japan Geriatrics Society (JGS) Joint Committee on Improving Care for Elderly Patients with Diabetes, 2017).

Physical exercise and diet are first recommended in the management of T2DM, given that there are numerous evidences to demonstrate that physical exercise, including aerobic and resistance training, improves glycemic control and insulin sensitivity (Willey and Singh, 2003; Way et al., 2016). However, the effects of physical exercise on cognition are shown to be inconsistent among older adults with T2DM (Zhao et al., 2018). In a small randomized controlled trial (RCT), Baker et al. demonstrated that aerobic exercise, continued over 6 months, improved executive function among 28 older adults with glucose intolerance (Baker et al., 2010). Recently, an exploratory analysis from the Lifestyle Interventions and Independence for Elders trial demonstrated that physical activity interventions may benefit cognitive function in older adults with diabetes, but not in those without (Espeland et al., 2017). These results indicate that older adults with T2DM are more likely to benefit from physical exercise interventions, thus suggesting the need for further intervention trials.

In older adults with T2DM, dietary intake and nutritional status are also associated with cognitive decline and incident dementia. The Japanese Elderly Diabetes Intervention Trial, which is a longitudinal study, showed that low intakes of carotene, vitamin B2, pantothenate, calcium and green vegetables predicted cognitive decline among male older adults with diabetes during a 6-year follow up (Araki et al., 2017). Nam et al. demonstrated that lower body mass index (<18.5) at baseline and weight loss after diagnosis of T2DM increased risk of incident all-cause of dementia, especially AD, during an average 3.5-year follow up. Weight gain also increased risk of incident all-cause dementia (Nam et al., 2019). Although these observational studies highlight needs of monitoring and interventions on diet and nutritional status for prevention of dementia, there still lacks evidence from a dietary intervention trial.

Again, several large multi-domain prevention trials have provided the evidence that interventions simultaneously targeting multiple risk factors for dementia in older adults, especially in those at increased risk of dementia, may slow cognitive decline and reduce cognitive impairment (Ngandu et al., 2015; Moll van Charante et al., 2016; Andrieu et al., 2017). However, to date, no multi-domain prevention trial for prevention of cognitive decline has been conducted with a focus on older adults with T2DM.

Therefore, the aim of this trial, named the Japan-Multi-domain Intervention Trial for Prevention of Dementia in Older Adults with Diabetes (J-MIND-Diabetes), is to investigate whether multi-domain intervention (consisting of management of metabolic and vascular risk factors, physical exercise and self-monitoring of physical activity, nutritional guidance, and promoting social engagement) may prevent the progression of cognitive decline among T2DM patients with mild cognitive impairment. This manuscript describes the study protocol for the J-MIND-Diabetes trial, and conforms to the Standard Protocol Items: Recommendations for Interventional Trials (SPIRIT) 2013 statement (Supplementary Table 1).

## Methods and Materials

### Study Design and Setting

The J-MIND-Diabetes study was designed as a 18-month, open-labeled, randomized, controlled, multicenter trial of multi-domain intervention targeting modifiable risk factors for dementia among T2DM patients with cognitive impairment. To be organized by a central coordinating center at the National Center for Geriatrics and Gerontology (NCGG), this study involves 16 centers located in Japan. This study will randomize 300 T2DM patients with cognitive impairment into intervention or control groups. The multi-domain intervention will address the following 4 domains: (1) management of metabolic and vascular risk factors (diabetes, hypertension, and dyslipidemia); (2) physical exercise and self-monitoring of physical activity; (3) nutritional guidance; and (4) promoting social participation. The control group will receive usual diabetes care and general instructions on dementia prevention. The primary and secondary outcomes will be assessed at baseline, 6, and 18 months in both groups (see the study flow diagram shown in Figure 1).

**Figure 1 F1:**
[figure not shown]
Study flow of the Japan-multi-domain intervention trial for prevention of dementia in older adults with diabetes (J-MIND-Diabetes).

### Ethic Committee Review and Approval

All study procedures have been reviewed and approved by the Institutional Review Boards (IRBs) at all participating institutions, and this trial has been registered on the University Hospital Medical Information Network Clinical Trials Registry (UMIN-CTR) as number UMIN000035911. The purpose, nature, and potential risks of this trial will be fully explained to the participants, and all participants will provide written informed consent before participating in the trial.

### Eligibility Criteria (Inclusion/Exclusion Criteria)

Table 1 shows the inclusion and exclusion criteria for the J-MIND-Diabetes trial. In order to focus on those at increased risk of dementia, this trial focuses on T2DM patients who are classified into category II (mild cognitive impairment to mild dementia) based on the “Glycemic Targets for Elderly Patients with Diabetes” as they were put forth by the JDS/JGS Joint Committee (Japan Diabetes Society (JDS)/Japan Geriatrics Society (JGS) Joint Committee on Improving Care for Elderly Patients with Diabetes, 2017). Therefore, patients are found eligible for the J-MIND-Diabetes trial if they (1) are diagnosed with T2DM, (2) are aged 70-85 years at enrollment, (3) have no or mild impairment of basic activities of daily living (ADL) [Barthel index (Mahoney and Barthel, 1965) score of 80 or more], (4) are mildly cognitively impaired [the Japanese version of the Montreal Cognitive Assessment (MoCA-J) (Fujiwara et al., 2010) score of less than 26], (5) have a Mini-Mental State Examination (MMSE) (Folstein et al., 1975) score of 21-30, (6) are outpatients or those who have a stable clinical course for more than 4 weeks after their last hospitalization or institutionalization and whose medical examination classification need no change during the monitoring period, (7) are accompanied by a co-participant (study partner), and (8) provide written informed consent on their own or via their study partners.

**Table 1 T1:** Inclusion and exclusion criteria for the J-MIND-Diabetes trial.

**Inclusion criteria**
1.Patients with type 2 diabetes mellitus
2.Patients aged 70–85 years at enrollment
3.Patients with no or mild impairment of basic activities of daily living (Barthel Index score of 80 or more)
4.Patients with a Japanese version of the Montreal Cognitive Assessment score of less than 26
5.Mini-Mental State Examination score, between 21 and 30
6.Outpatients or those exhibiting a stable clinical course for more than 4 weeks after their last hospitalization or institutionalization and whose medical examination classification need no change during the monitoring period
7.Patients accompanied by a co-participant (study partner)
8.Those who gave written informed consent
**Exclusion criteria**
1.Patients with extremely poor metabolic control (fasting plasma glucose level over 250 mg/dl; or moderate or severe urinary ketone levels).
2.Patients with new hemorrhage in the ocular fundus caused by proliferative retinopathy
3.Patients with renal failure
4.Patients with ischemic heart disease and cardiopulmonary disorders
5.Patients with bone or joint disease
6.Patients with acute infectious disease
7.Patients with diabetes gangrene.
8.Patients with severe autonomic neuropathy
9.Patients with decreased cognitive function due to Parkinson's disease, apoplexy, Huntington's disease, normal pressure hydrocephalus, brain tumors, progressive supranuclear palsy, corticobasal degeneration, multiple system atrophy, aphasia, epilepsy, subdural hematoma, encephalitis/meningitis, multiple sclerosis, or head injury
10.Patients with any local lesion, such as cerebral infarction(s) detected by CT or MRI before enrollment, that may greatly affect cognitive function
11.Patients with a history of major depression, bipolar disorder, schizophrenia, or alcohol/drug abuse; those with current serious or unstable disease
12.Patients unsuitable for treatment due to vitamin B1/B12 and/or folate deficiency, syphilis, or thyroid dysfunction
13.Patients deemed ineligible for enrollment by their responsible investigator or co-investigator at participating institutions

*J-MIND-Diabetes, japan-multi-domain intervention trial for prevention of dementia in older adults with diabetes*.

Patients are to be excluded if they have extremely poor metabolic control (fasting plasma glucose level, over 250 mg/dl; or moderate urinary ketone values) that would preclude or restrict exercise, hemorrhage in the ocular fundus caused by proliferative retinopathy, renal failure, ischemic heart disease and cardiopulmonary disorders, bone or joint disease, acute infectious disease, diabetes gangrene, and severe autonomic neuropathy (Table 1). Moreover, patients are to be excluded if they have diseases which greatly affect their cognitive function (Parkinson's disease, apoplexy, Huntington's disease, normal pressure hydrocephalus, brain tumors, progressive supranuclear palsy, corticobasal degeneration, multiple system atrophy, aphasia, epilepsy, subdural hematoma, encephalitis/meningitis, multiple sclerosis, head injury, any local lesion detected by brain computed tomography (CT) or magnetic resonance imaging (MRI), major depression, bipolar disorder, schizophrenia, alcohol/drug abuse and untreatable vitamin B1/B12 and/or folate deficiency, syphilis, or thyroid dysfunction) (Table 1).

### Enrollment and Assessment Procedures

#### Recruitment

Since T2DM outpatients who fall under category II based on the JDS/JGS Joint Committee's guidelines (Japan Diabetes Society (JDS)/Japan Geriatrics Society (JGS) Joint Committee on Improving Care for Elderly Patients with Diabetes, 2017) and have mild cognitive impairment comprise the target population, their initial eligibility will be determined based on their clinical charts by the investigators. Then, potentially eligible patients with T2DM aged 70-85 years will be assessed for cognitive function [MoCA-J (Fujiwara et al., 2010) and MMSE (Folstein et al., 1975)] and basic ADL [Barthel Index (Mahoney and Barthel, 1965)], with their final eligibility determined by the investigators and clinicians according to the inclusion and exclusion criteria.

#### Assessment

All subjects will complete neuropsychological tests, comprehensive geriatric assessments (CGA), and blood and urinary tests at baseline, as well as at 6- and 18-month follow-up. Additionally, brain MRI or CT will be performed by the scanner available at each institution at baseline and 18-month follow-up to detect any local lesion such as cerebral infarctions that can greatly affect cognitive function. Adherence to the intervention programs and adverse events will be also monitored during this trial. The timeline for scheduled assessments following the SPIRIT guidelines is shown in Figure 2.

**Figure 2 F2:**
[figure not shown]
Timeline for participants in the J-MIND-Diabetes trial. ^*^: Non-mandatory, -t_1_: visit within 8-week before the day of allocation, t_1_…t_n_: visit to the hospital during the study period. CT, computed tomography; J-MIND-Diabetes, japan-multi-domain intervention trial for prevention of dementia in older adults with diabetes; MRI, magnetic resonance imaging; SPECT, single photon emission computed tomography.

Psychologists at each institution were trained in the implementation and scoring methods of neuropsychological tests by participating in the training session held at the NCGG. Moreover, scoring for the Rey-Osterrieth Complex Figure Test (ROCFT) (Strauss et al., 2006) will be conducted by a single psychologist from the NCGG to minimize variability in scoring between neuropsychologists.

#### Primary Outcome: Cognitive Change at 18-Month Follow-Up (Composite Score)

The primary outcome is change from baseline at 18 months in a global composite score using several neuropsychological tests (Table 2), which include tests of global cognitive function [MoCA-J (27), MMSE (Folstein et al., 1975)]; memory [ROCFT (Strauss et al., 2006), delayed recall test of a 10-word list derived from the Alzheimer's Disease Assessment Scale-cognitive subscale (ADAS-Cog) (Mohs and Cohen, 1988)]; attention [Wechsler Adult Intelligence Scale (WAIS) Digit Span (Wechsler, 1997)]; executive function/processing speed [Trail Making Test (TMT) (Lezak, 2004), Digit Symbol Substitution Test (DSST) (Wechsler, 1997), Letter word fluency test (Lezak, 2004)]. The composite score will be generated by averaging the Z scores of each neuropsychological test standardized with baseline means and standard deviations (SDs) for each test from the intention-to-treat population. A Z score of −1, for example, represents a score that is 1 SD below the baseline mean. A one-point decrease on the composite score indicates an average decline of 1 SD across the neuropsychological tests.

**Table 2 T2:** Primary outcome measures in the J-MIND-Diabetes trial.

**Domain**	**Neuropsychological test**
Global cognitive function	• Japanese version of the montreal cognitive assessment (Fujiwara et al., 2010) • Mini-mental state examination (Folstein et al., 1975)
Memory	• Rey-osterrieth complex figure test (Strauss et al., 2006) • Word-list memory [ADAS-cog (Mohs and Cohen, 1988)]
Working memory	• Digit span test [WAIS-III (Wechsler, 1997)]
Processing speed	• Digit symbol substitution test [WAIS-III (Wechsler, 1997)]
Attention	• Trail making test part A (Lezak, 2004)
Executive function	• Trail making test part B (Lezak, 2004) • Letter word fluency test (Lezak, 2004)

*ADAS-cog, alzheimer's disease assessment scale-cognitive subscale; J-MIND-Diabetes, japan-multi-domain intervention trial for prevention of dementia in older adults with diabetes; WAIS, wechsler adult intelligence scale*.

#### Secondary Outcomes

##### Cognitive Change at 6-Month Follow-Up (Composite Score) and Change in Scores of Each Neuropsychological Test at 6-/18-Month Follow-Up

Secondary outcomes related to cognitive changes are: change from baseline at 6 months in the global composite score described for the primary outcome; and change from baseline in scores of each neuropsychological test at 6-/18 month follow-up.

##### Improvement in Outcomes Related to T2DM

Metabolic control: In blood tests performed at baseline and 6-/18-month follow-up, the participants will be assessed for glycated hemoglobin (HbA1c), glycoalbumin, fasting blood glucose levels, and fasting blood insulin levels. Additionally, at baseline and 18-month follow-up, they will also be evaluated for SD of blood glucose levels, mean amplitude of glycemic excursions (MAGE), continuous overall net glycemic action (CONGA), and mean of daily differences (MODD) (Inchiostro et al., 2013) by using the FreeStyle Libre Pro system (Abbott Diabetes Care, Tokyo, Japan), a continuous glucose monitoring (CGM) system capable of providing records of glucose levels, trends, and patterns in each individual for up to 14 days. Moreover, the averaged percentage of time each participant spent in hypoglycemia (<70 mg/dL) will be also calculated.Self-reported hypoglycemic events: Participants will be assessed for hypoglycemic events by asking the following questions: “Did you experience any hypoglycemia episode that required the assistance of another person in the past year?” (Yes/No); “Did you experience any symptoms, such as sweating, palpitation, or trembling, in the past year?” (Yes/No); and “Did you experience any symptoms, such as lightheadedness, unsteadiness, dizziness, or visual disturbance, in the past year?”Microangiopathy and macroangiopathy: Participants will be assessed at baseline and at follow-up for microangiopathy including retinopathy, nephropathy, and neuropathy. Participants will be assessed for retinopathy categorized into five stages (Wilkinson et al., 2003): (1) no apparent retinopathy, (2) mild non-proliferative retinopathy, (3) moderate non-proliferative retinopathy, (4) severe non-proliferative retinopathy, (5) proliferative diabetic retinopathy. They will also be assessed for presence or absence of edema in the macula of the retina as well as for visual acuity by the Landolt Ring Test. Participants will be assessed for diabetic nephropathy categorized into five stages based on urinary albumin (mg/gCr), urinary protein (g/gCr), or estimated glomerular filtration rate (eGFR, mL/min/1.73m2) (Japan Diabetes Society, 2016): (1) Pre-nephropathy, (2) incipient nephropathy, (3) overt nephropathy, (4) kidney failure, (5) dialysis therapy. They will also be assessed for diabetic neuropathy using the Achilles tendon reflex test and vibration testing with a 128-Hz graduated tuning fork. Again, they will also be assessed for macroangiopathy, including ischemic heart disease, stroke, and peripheral vascular disease, based on their clinical charts and MR or CT imaging (Japan Diabetes Society, 2016).

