##### Management of Metabolic and Vascular Risk Factors

While participants will be treated for T2DM, hypertension, and dyslipidemia in accordance with clinical guideline recommendations in Japan, they will be treated for T2DM based on the Treatment Guidelines for Elderly Patients with Diabetes Mellitus 2017 issued by the JDS/JGS Joint Committee (Japan Diabetes Society (JDS)/Japan Geriatrics Society (JGS) Joint Committee on Improving Care for Elderly Patients with Diabetes, 2017), which recommend that the glycemic target (HbA1c) be determined for each patient by taking into account his or her background characteristics and health status and classifying the patient into 1 of the following 3 categories: category I (intact cognitive function and ADL), category II (mild cognitive impairment to mild dementia or impairment of instrumental ADL), and category III (moderate or severe dementia, impairment of basic ADL, or presence of multiple comorbidities). As a specific feature of these categories, the lower limit of each glycemic target is specified for those receiving drugs associated with high risk of severe hypoglycemia, for example, insulin, sulfonylureas, and glinides. In this trial focused on subjects classified as category II, therefore, the upper limit of the glycemic target is to be set at 7.0% for patients not receiving these drugs, while the upper and lower limits of the glycemic target are to be set at 8.0% and 7.0%, respectively, for those receiving these drugs. Additionally, those in the intervention group will undergo CGM assessments to avoid hypoglycemia and glycemic fluctuations; while, likewise, those in the control group will undergo CGM assessments, clinicians will be blinded to the results of CGM assessments in these patients.

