#### Randomization and Blinding

In this open-label intervention study, participants will be centrally randomized at a 1:1 allocation ratio into intervention and control groups using the stratified permuted-block randomization methods based on the following stratification variables:

Institutions (1–15 institutions).Age at enrollment (70–77 years vs. 78–85 years).Glycemic control relative to the glycemic targets recommended by the JDS/JGS joint committee (optimally controlled vs. poorly or excessively controlled).Drugs potentially associated with severe hypoglycemia such as insulin, sulfonylureas and glinides (those receiving these drugs vs. those not receiving these drugs).

The randomization sequences will be generated by a trial statistician ([name]) by using Proc Plan in SAS version 9.4 (SAS Institute, Cary, NC, USA). Study participants and research staff including investigators and clinicians at each institution will be unaware of the randomization sequences and block size. Research staff responsible for primary outcome data collection will also be blinded to group assignment, to which, however, the intervening research staff and the participants will be not blinded.

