#### Data Analyses

Data will be presented as means, medians, standard deviations, ranges and interquartile ranges for continuous and ordinal variables, and counts and percentages for categorical variables. Differences in baseline clinical characteristics between the intervention and control groups will be examined for significance by using the *t*-test or the Mann-Whitney U test for continuous variables and by the chi-squared test or the Fisher's exact test for categorical variables, as appropriate.

To evaluate differences in cognitive changes from baseline at 18-month follow-up between the intervention and control groups, the mixed-effects model for repeated measures (MMRM) with an unstructured covariance structure will be conducted using groups, time of the visit, group by time interaction, and baseline composite cognitive score as covariates. For the secondary continuous variables, the same analyses using MMRM will be performed. For the secondary categorical variables, logistic regression analyses or chi-squared tests will be conducted as appropriate. Frequencies of adverse events and serious adverse events will be summarized and compared between the intervention and control groups by using the chi-squared test or the Fisher's exact test.

All statistical analyses will be performed using SAS 9.4 (SAS Institute, Cary, NC, USA). *P*-values <0.05 will be considered statistically significant.

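### Fasting insulin is a secondary outcome for all participants although insulin users are enrolled, so the pooled comparison mixes endogenous with injected insulin and cannot be read cleanly as improved metabolic control

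*Protocol article*

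**What the plan says.** Four parts of the protocol article bear on this.

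- **Outcome.** In the T2DM part of the secondary outcomes, under metabolic control, the participants are measured for HbA1c, glycoalbumin, "fasting blood glucose levels, and fasting blood insulin levels". The times are baseline, 6 and 18 months. No subgroup is named, and the section heading presents these outcomes as improvement.
- **Analysis.** Data Analyses: "For the secondary continuous variables, the same analyses using MMRM will be performed". The model described there has group, visit, group-by-visit interaction and the baseline score. It has no term for insulin use and no restriction by insulin use.
- **Population.** The first inclusion criterion is "Patients with type 2 diabetes mellitus", and no exclusion criterion mentions insulin treatment. Randomization and Blinding stratifies on "Drugs potentially associated with severe hypoglycemia such as insulin, sulfonylureas and glinides", as one yes/no factor. The section on metabolic and vascular risk factors sets a separate glycemic target range for patients on these drugs. Insulin users are therefore expected in the trial.
- **Care by arm.** The same section uses CGM in the intervention group to avoid hypoglycemia and glucose swings. Control patients also wear the sensor, but their clinicians do not see the results.

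C-peptide appears neither under metabolic control nor in the list of blood and urinary markers.

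**The concern.** In a patient who does not inject insulin, a fasting insulin level reflects the patient's own secretion. In a patient who does, it can also reflect the injected product, to a degree that depends on the preparation, the time since injection and whether the assay detects that product. One mean difference over both groups has no single meaning, and no listed marker separates the two sources.

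Randomisation does not remove this. It balances insulin use at baseline, and the stratification helps only for the pooled drug class. It does not hold injected insulin equal afterwards. Clinicians see CGM results in one arm only, so insulin treatment may develop differently by arm. A lower mean in the intervention arm could then be reported as a metabolic improvement when part of it is less injected insulin. The misreading is foreseeable, because the Introduction names insulin resistance among the mechanisms of particular interest.

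**Working it through.** **1. The plan's own figure.** The article gives no figure for fasting insulin. Its only sizing is for MMSE change (Sample Size section): −0.33 (SD 2.58) against −1.45 (SD 3.55), two-sided 5%, power 80%.

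- Difference: 1.45 − 0.33 = 1.12.
- Pooled SD: √((2.58² + 3.55²)/2) = 3.103.
- n per arm: 2 × (1.960 + 0.842)² × 3.103² / 1.12² ≈ 120.5, so 121 per arm and 242 in total.

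This reproduces the stated 242. The point does not depend on it. Only the 121 per arm, and the standardised effect 1.12/3.103 = 0.361 that this number detects with 80% power, are borrowed for step 3.

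**2. What the pooled difference estimates.** Let q be the share of insulin users, D_N the arm difference in non-users and D_U that in users. Then

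pooled difference = (1 − q) × D_N + q × D_U.

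- If D_N = 0 and insulin dosing shifts in one arm, the pooled difference is q × D_U. At q = 0.20 that is one fifth of the users' difference, with no change in anyone's endogenous insulin.
- If D_U carries no interpretable effect, the pooled difference is (1 − q) × D_N: 90%, 80%, 70%, 60% or 50% of the non-user effect for q = 10% to 50%.

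**3. Illustration of power.** Assumptions, none from the article: 121 evaluable per arm, standardised effect 0.361 in non-users, zero in users, simple two-group comparison.

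| Share of users (assumed) | Pooled, equal SD | Pooled, users' SD doubled | Non-users only |
|---|---|---|---|
| 10% | 71% | 60% | 76% |
| 20% | 61% | 43% | 71% |
| 30% | 50% | 30% | 65% |
| 40% | 39% | 21% | 59% |
| 50% | 29% | 14% | 51% |

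The pooled comparison is diluted but still carries information.

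**4. Precision alone.** Let k be the SD in users divided by the SD in non-users. The pooled variance relative to non-users is v = (1 − q) + q·k², and

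SE(all patients) / SE(non-users only) = √(v × (1 − q)).

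- k = 1: √0.85 = 0.92 at q = 0.15 and √0.65 = 0.81 at q = 0.35. The pooled analysis has the smaller SE.
- Break-even: k² = (2 − q)/(1 − q). At q = 0.15, 1.85/0.85 = 2.18, so k = 1.48. At q = 0.35, 1.65/0.65 = 2.54, so k = 1.59.
- k = 2, q = 0.15: v = 1.45, ratio 1.11. k = 5, q = 0.35: v = 9.4, ratio 2.47.

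Restriction lowers the SE only if users' values are more than about 1.5 to 1.6 times as variable. The article gives nothing to place k. The formula also uses raw variance, whereas the planned model adjusts for baseline.

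**The case against.** The strongest objection is that this is analysis-plan detail. The article condenses a longer protocol. It says who is measured and gives one general sentence for many secondary variables. It never says of fasting insulin in particular that all patients enter the analysis, and a restriction may stand in a document not shown. That is fair, and it limits the point to the rule as published. But the article does state both the measured group and the rule, and together they give a pooled analysis.

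A second objection is that a randomised difference in circulating insulin is validly estimated, and that a change in injected insulin is part of the intervention's effect. This also stands: the problem is one of interpretation, and bias is the wrong word for it. It remains a problem because the outcome is listed as metabolic improvement.

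Two stronger readings are tempting and not supported:

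- A reader might infer that the comparison measures no metabolic effect at all. In non-users the value stays interpretable, and the share of users is unknown.
- A reader might infer a known loss of precision, such as an SE 1.1 to 2.5 times larger. That range follows only if users' SD is assumed to be 2 to 5 times that of non-users, which lies wholly above break-even.

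Nor does the article plan a resistance or secretion index from fasting insulin, so none is at fault.

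**Conclusion.** The point holds as a minor one. Under the published rule, fasting insulin pools endogenous insulin in non-users with a possible mix of endogenous and injected insulin in users. An arm difference may partly reflect a change in injected insulin. The result cannot be read cleanly as improved metabolic control.

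The size is open. It depends on the share of insulin users, the assay and the preparations, none of which the article states, and on whether insulin treatment diverges by arm, which the one-sided use of CGM makes possible but does not show. The dilution and power figures are illustrations under assumed shares and a zero effect in users.

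One secondary outcome is affected. The primary outcome, the sample size of 242 (300 with dropout), and HbA1c, glycoalbumin, fasting glucose and the CGM indices are untouched.

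**What to change.** State in the analysis section, or confirm in the analysis plan:

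- The main analysis of fasting insulin is the planned MMRM in patients not receiving insulin at baseline. This subset is defined before randomisation, so the comparison within it remains randomised.
- Baseline insulin use is taken from the drug record. The stratum cannot supply it, because it pools insulin with sulfonylureas and glinides.
- A sensitivity analysis covers patients in this subset who start insulin later, for example by setting their later values to missing. State that starting insulin is a post-randomisation event which the intervention may influence, so such missingness may be informative, and report the number by arm.
- For patients on insulin at baseline, report insulin use by arm at follow-up. Report dose only if it is recorded, since the article does not list it as collected.

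The cost is a few sentences, with no new sample or assay and no change to treatment. The downsides are a smaller n, possibly a larger SE if users' values are no more variable than the rest, and a result that applies only to patients not on insulin. Fixing this before the data are seen also avoids a post-hoc choice of subset in an open-label trial.
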